#### Strategy to guarantee the targeted sample size

In case of insufficient patient enrollment by the GPs, local study centers will recruit additional GPs who will be randomly allocated to one of the two study arms by the independent statistician (see above). Patients in the intervention group at each site will receive treatment as specified in the GermanIMPACT treatment plan manual. Patients in the control group at each site will receive treatment as usual (as agreed on with their GP without involvement of a CM and MHS). As the collaborative care approach was developed to support the treatment of depression in older adults in general practices, the comparison to a treatment-as-usual group was chosen to examine if ancillary care has an additional effect on symptom remission. This approach is analogous to the IMPACT study developed in the United States; since GermanIMPACT is an adaption of the original study, the same comparative conditions were chosen.

### Blinding

Since there is no placebo condition, blinding after assignment is impossible. However, patients in the intervention and control groups only receive information pertaining to their respective study arm so that each group is unaware of the condition of the other group. In both groups, patient outcomes are collected by the data management team (assessors) to prevent the involvement of the CM in patient assessment. The assessors will contact patients in both study arms repeatedly to ensure a low rate of missing data. Due to the pseudonymization process, the statistician will, at all times, be unaware of the identity of the participating practices. Moreover, the statistician will analyze the primary and secondary outcome data without knowledge of the subjects’ allocation to the study arms. For additional analyses of the treatment process, this kind of blinding is not possible.

### Intervention

#### Warm hand-off

Upon inclusion, patients in the intervention group schedule an appointment with their GP and their assigned CM at the GP’s office. The familiarity of the setting reduces access barriers to mental health services and increases patient compliance. It is crucial for the intervention process that the CM be personally introduced to the patient by the GP as a member of the treatment triad; the integration of the CM in the treatment plan should not be perceived as an external referral.

#### Care manager-patient contact

In a 60-minute face-to-face session, the CM provides a short overview of the 12-month treatment period and introduces the patient to the basic intervention techniques and the patient workbook. A semi-structured interview serves to assess the patient’s current health status and behavior, symptoms, medication, and psychosocial stressors and resources; the answers serve as a starting point for the individual intervention plan. As a first task, the patient is encouraged to keep an activity journal for the next seven days.

One week later, the initial session is followed by a 60-minute telephone session during which behavioral activation is revisited and patients are sensitized to the positive relationship between activity and mood improvement. With the help of the activity journal, a list of pleasant activities is created from which the patient is encouraged to choose two and to integrate them into their daily routine. After this second session, 30-minute telephone sessions are held every other week. Every session consists of a short symptom assessment via the PHQ-9 and a short interview including questions about GP visits, medication effects and adherence, and experiences with the behavioral activation tasks. Potential barriers for activity planning and realization are carefully analyzed and new tasks for the next 14-day period are selected accordingly. Due to the regular contact between the CM and patient, the CM can monitor and record deviances from the planned intervention and react instantly to difficulties regarding adherence to the protocol.

The PHQ-9 questionnaire is used throughout the intervention to assess the current depressive status and to monitor treatment progress. Research shows that administering the PHQ-9 over the phone leads to similar results as an in-person assessment or self-administration [34]. Every eight weeks, a treatment evaluation session is held. Depending on symptom development, the CM can continue the intervention without changes or offer the patient different options for treatment adaptation according to a stepped-care algorithm. In addition to medication-related changes (for example, changes in medication dosage) initiated by the GP and the continuance of activity planning, the CM can provide training sessions focused on problem-solving techniques. This is a brief behavioral intervention intended to reduce depressive symptoms by teaching patients how to systematically solve psychosocial problems. For details on this specific intervention, see Hegel *et al.*[35]. Figure 3 summarizes the 12-month intervention process.

**Figure 3 Fig3:**
[figure not shown]
**Sequence of intervention sessions provided by the care manager (total intervention period = 12 months).**

#### Stepped care

Participating GPs are encouraged to start or continue the treatment of depression according to clinical guidelines, including the prescription of antidepressants. They can contact the supervising MHS at any time for consultation.

The continuous assessment of depressive symptoms by the CM allows for the close monitoring of treatment results. CMs and supervising MHSs meet regularly to discuss every patient’s status. Every eight weeks, the need for treatment changes is carefully evaluated. The patient’s PHQ-9 score at baseline serves as the reference parameter for symptom changes at the eight-week intervals. Recommendations for treatment adaptation are based on a stepped-care algorithm as displayed in Table 1. The stepped-care approach allows for modifications of the intervention for each individual participant according to his or her current health status. The criteria for choosing the best option within the possibilities of the stepped-care algorithm are the professional assessment of the GP and the MHS as well as the personal preference of the patient.

**Table 1 Tab1:** **GermanIMPACT stepped-care algorithm**

Change of current PHQ score compared to baseline	Recommended step
**Improvement of less than 50%** (including no improvement and worsening of symptoms)	a) Medication-related changes (initiated by the GP) including initiation if patient is currently without medication, or
	b) Training of problem-solving techniques provided by the care manager: two face-to-face sessions, four telephone sessions (approximately 45 minutes each); afterwards resumption of telephone sessions at two-week intervals
**Improvement of 50% or more**	No treatment changes
**PHQ-9 score <5** (remission)	c) Discussion of a relapse prevention and emergency plan
	d) Reduction of telephone sessions to four-week intervals; in case of relapse, resumption of telephone sessions at two-week intervals

### Outcome measures and assessment

#### Primary outcome

Primary outcome is the change of the PHQ-9 score [36] as a measure of depressive symptoms over the course of the study from baseline to the end of intervention. In line with similar studies [19, 25, 31], response to treatment is defined as a symptom reduction of 50% or more, and remission is defined as a PHQ-9 score below 5. The PHQ-9 is considered a valid instrument for subgroups of primary care patients with a high prevalence of major depressive episodes [37].

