**Methods/Design:**

The study will be conducted as a cluster-randomized controlled trial comparing the development of depressive symptoms in primary care patients who either receive treatment as usual (control arm) or treatment according to the GermanIMPACT model (intervention arm). In two German cities (Freiburg and Hamburg), a total of 60 general practice offices will be selected and randomized. Each general practice office will be asked to enroll five patients into the trial who are 60 years of age or older and who show moderate depressive symptoms in the scope of a diagnosed depressive episode, recurrent depressive disorder, or dysthymia. General practices in the control arm will provide treatment as usual; general practices in the intervention arm will work closely with a specially trained care manager and a supervising mental health specialist. Evidence-based elements of the treatment plan manual include patient education, identification and integration of positive activities into the daily routine, relapse prevention, and training of problem-solving techniques as needed. The intervention period per patient will be one year. Data will be collected at baseline, 6, and 12 months. Primary outcome is the patient-reported change of depressive symptoms (Patient Health Questionnaire, PHQ-9). Secondary outcomes include measures of quality of life, anxiety, depression-related behavior, problem-solving skills, resilience, and an overall economic evaluation of the program.

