### Sample size

The remission of depressive symptoms as measured by the Patient Health Questionnaire PHQ-9 at 12 months’ follow-up will be the primary outcome measure of the study. A randomized controlled trial investigating the effectiveness of the IMPACT program in the United States yielded a remission rate of 25.0% in the intervention group and 8.3% in the control group [19]. Assuming these remission rates in our trial along with a conventional value for the type I error rate (α = 0.05), a two-sided test on inequality of proportions requires 85 patients per arm (170 in total) to detect this effect with a power of 0.8 (type II error rate β = 0.2). Calculations were done with STATA 12.1 [33]. However, in order to account for the hierarchical structure of the collected data due to the cluster-randomized design, it must be considered that patients treated by the same GP are likely to be more similar in terms of treatment response than patients treated by different GPs. Assuming a fixed number of included GPs (30 per arm, 60 in total) and an amount of variance in the outcome explained by differences between physicians rather than between patients (intraclass correlation coefficient of 10%), the factor of the necessary increase in sample size (so-called ‘design effect’) due to the clustered design yields 1.46, increasing the required sample size to a total of 250 patients. This is the number needed for an appropriately powered per-protocol analysis (only completers are analyzed). To compensate for a conservatively estimated 15% loss to follow-up [19, 31], each participating GP will be instructed to include 5 patients in the study, amounting to a total of 300 patients allocated to the trial (150 per arm). The primary analysis will be performed in the intention-to-treat population, that is, all randomized patients will be included. In the intention-to-treat analysis, the higher number of patients is likely to be compensated for by a potential dilution of treatment effects, so that the power will be approximately the same as described for the per-protocol analysis.

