### Statistical analysis

The primary analysis will compare the proportion of patients remitted of depressive symptoms at the 12-month follow-up using a mixed-effects logistic regression model in the intention-to-treat sample (including all randomized patients). Treatment condition (intervention versus control) will be treated as a fixed effect. Baseline severity of depressive symptoms will be included as a covariate and variation among patient clusters (treated by the same GPs) will be modeled through random effects. Further binary outcomes will be modeled correspondingly. Continuous outcomes will be analyzed according to the same scheme, but in linear rather than logistic regression models. Item-level missing data in psychometrically sound instruments will be treated in compliance with the corresponding manuals. If no recommendations are available, the expectation-maximization (EM) algorithm will be used to impute up to 30% of missing item responses. Unit-level missing data (patients not providing data for a whole measurement point due to dropping out of the study, for example) will be imputed via the EM algorithm using existing information from the baseline and 6-month follow-up assessments. Further secondary analyses will include analyses in the per-protocol (completer) sample to test the robustness of the primary findings. No interim analysis is planned. Before the start of the analysis, a detailed statistical analysis plan (SAP) will be prepared by the responsible statistician. Intervention-related data are stored and analyzed separately. All analyses will be computed using Stata 12.1. Figure 4 provides a detailed overview of the study design.

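### The section headed Primary outcome names PHQ-9 change, the sample size and primary analysis use remission at 12 months, and nothing in the article ranks the two

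*Protocol article*

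**What the plan says.** Four places in the protocol article bear on the primary endpoint.

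- Abstract, Methods/Design: "Primary outcome is the patient-reported change of depressive symptoms", measured by the PHQ-9. Remission is not mentioned.
- Primary outcome section (under Outcome measures and assessment): "Primary outcome is the change of the PHQ-9 score [36", with change taken between baseline and the end of the intervention. The next sentence gives definitions: "response to treatment is defined as a symptom reduction of 50% or more, and remission is defined as a PHQ-9 score below 5". Neither is called primary there.
- Sample size section: "The remission of depressive symptoms as measured by the Patient Health Questionnaire PHQ-9 at 12 months’ follow-up will be the primary outcome measure". The calculation uses remission rates of 25.0% and 8.3%.
- Statistical analysis section: "The primary analysis will compare the proportion of patients remitted of depressive symptoms at the 12-month follow-up", by mixed-effects logistic regression in the intention-to-treat sample. Continuous outcomes go to linear models on the same scheme.

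The Secondary outcomes section does not list PHQ-9 change. Table 2 lists only the PHQ-9 under the primary outcome, without saying whether the score or remission is meant. The instrument and the primary time point (12 months) agree throughout.

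**The concern.** The same label is attached to two variables that differ in scale, effect measure and model: a mean difference from a linear mixed model, and an odds ratio from a logistic mixed model. Naming one primary outcome in advance is meant to settle which result decides whether the trial succeeded. Here a report headlining PHQ-9 change could cite the abstract and the Primary outcome section, and one headlining remission could cite the other two sections. The two results need not agree. The stated power covers only one of them.

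**Working it through.** **1. Which endpoint do alpha, power and sample size belong to?** Inputs from the Sample size section: 25.0% versus 8.3%, two-sided alpha 0.05, power 0.80, 85 per arm, design effect 1.46, 15% loss to follow-up.

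- Patients per arm for two proportions: 77 (pooled normal formula, no correction), 75 (unpooled), 74 (arcsine), 89 (continuity-corrected).
- Exact power of Fisher's test: 0.7944 at 84 per arm and 0.8002 at 85. The stated 85 is reproduced.
- Clustering: 170 × 1.46 = 248.2, stated as 250.
- Loss to follow-up: 250/0.85 = 294.1, so 295, taken up to 60 × 5 = 300.

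The whole chain is a remission calculation. No mean difference or SD for PHQ-9 change appears anywhere in the article.

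**2. Are the two endpoints really different?** The inclusion range is a PHQ-9 score of 10 to 14 (Recruitment of patients). A patient going from 14 to 5 improves by 9 points and is not remitted. A patient going from 10 to 4 improves by 6 points and is remitted. The endpoints can rank the same two patients in opposite order.

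**3. Error rate if the endpoint were picked after seeing the data.** Two tests, each at 5%, no true effect, at least one significant:

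- Independent tests: 1 − 0.95² = 9.75%, the upper limit for jointly normal test statistics.
- Jointly normal statistics with assumed correlation 0.5, 0.7 and 0.8: 9.1%, 8.3% and 7.8%.
- Simulation with 125 per arm, normal scores, clustering ignored, 8,000 runs per setting. Assumed: baseline SD 1.4, follow-up SD 5, correlation of baseline with follow-up 0 or 0.3, remission 8.3%, 16.65% or 25%. The two test statistics correlated at about 0.5 to 0.7 in absolute value, and at least one test rejected in 7.8% to 9.0% of runs.

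**4. Power if PHQ-9 change were the endpoint.** The effective number per arm is n = 125/1.46 = 85.6. This carries the design effect stated for remission over to the change score, which is an assumption. The difference detectable with 80% power is (1.960 + 0.842) × √(2/85.6) = 0.43 SD. For an assumed standardised difference d, power = Φ(d/√(2/n) − 1.96), with √(2/85.6) = 0.153:

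| Assumed d | Power, n = 125/1.46 = 85.6 | Power, n = 150/1.46 = 102.7 |
|---|---|---|
| 0.3 SD | 50% | 58% |
| 0.4 SD | 74% | 82% |
| 0.5 SD | 90% | 95% |

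The last column uses all 150 patients allocated per arm. Depending on the true effect, power for the change score lies below or above the stated 80%. The article gives no basis for choosing a row.

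**The case against.** The strongest reply is that the article does fix the decisive test. Only one analysis is labelled primary, and it is the remission comparison, with its model, covariate, random effect and population specified. Alpha, power and sample size are stated once, for remission. The abstract and the Primary outcome section name a variable but attach no test to it, and the line on linear models is a general rule for continuous outcomes. The Primary outcome section also supplies the remission cut-off that the primary analysis needs, so it might be read as naming the construct, with remission as the way it is tested. Finally, a detailed SAP is promised before analysis and could confirm the endpoint.

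Most of this stands. A reader might infer that nothing says which endpoint governs, that the 5% test is therefore open, and that the trial may declare success on either endpoint with an error rate near 9%. The article does not support that: it plans no second primary test and no either/or success rule.

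The reply does not remove the conflict. The Sample size and Primary outcome sections each make a positive statement about what the primary outcome is, and they name different variables. Nowhere does the article say that change is to be read as remission, or that PHQ-9 change is secondary. This is contradiction, not detail lost in condensing. A later SAP could settle the choice but would not correct the published text.

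**Conclusion.** The article contradicts itself on the primary outcome. The powered test and the labelled primary analysis both point to remission at 12 months, while the section that should define the primary outcome, and the abstract, name change. The harm lies in reporting: either result could be headlined with support from the protocol.

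The 8 to 9% false-positive chance (limit 9.75%) assumes that the endpoint is selected after the results are seen, and within that limit it depends on the assumed correlation between the tests. It does not describe the plan as written. The stated 80% power applies to remission only. The power figures for PHQ-9 change rest on assumed standardised effects and on the same design effect holding for the change score.

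**What to change.** In the abstract and the Primary outcome section, name remission (PHQ-9 below 5) at 12 months as the sole primary outcome, matching the Sample size and Statistical analysis sections. List PHQ-9 change (baseline-adjusted linear mixed model with a random effect for practice) and response under Secondary outcomes, and label the PHQ-9 rows of Table 2 to match. Use the same wording in the SAP before analysis begins.

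The cost is a wording correction. Alpha stays at 0.05 and the numbers stay at 85 per arm before clustering, 250 and 300. No further data are needed. The Trial status section expected data collection to run until September 2015, so at publication there was time to correct this before the analysis. If the sponsor prefers PHQ-9 change as primary, the cost is higher: the article would need a stated mean difference and SD, a new sample size calculation and a rewritten primary analysis.

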#### Assessment

Data are collected at baseline (t_0_), after 6 months (t_1_), and after 12 months (t_2_ = end of intervention, primary time of assessment). Patients in the intervention and control group will receive pseudonymous questionnaires by mail and are asked to complete and return them to the GermanIMPACT data management team. Table 2 shows an overview of the outcome measures, instruments, and times of assessment.

**Table 2 Tab2:** **GermanIMPACT outcome measures, instruments, and times of assessment**

Month	0		6		12*
Time of assessment	t_0_		t_1_		t_2_
**Primary outcome**					
Depression (PHQ-9)	X		X		X
**Secondary outcomes**					
Sociodemographic data	X	partial		partial	
Comorbidity (CDI, modified**)	X		–		X
Anxiety (GAD-7)	X		X		X
Pain (CPG, modified**)	X		X		X
Resource utilization (FIMA)	X		X		X
Preference-based quality of life (EQ-5D)	X		X		X
Resilience (RS-13)	X		X		X
Depression-related behavior (Ludman *et al*. [44], modified**)	X		X		X
Problem-solving skills	X		X		X
Current life situation	X		X		X
**Intervention group only**					
Evaluation of intervention	–		–		X
Therapy preference questionnaire	X		–		–
Depression (PHQ-9) - additional measures	–	each session	–	each session	–

*Primary time of assessment (t_**2**_) after intervention.

**Linguistic and culture-specific modifications

*Abbreviations:* PHQ-9, the Patient Health Questionnaire; CDI, the Comorbidity Disease Index; GAD-7, the seven-item Generalized Anxiety Disorder Scale; CPG, the Graded Chronic Pain Scale; FIMA, Fragebogen zur Inanspruchnahme medizinischer und nicht-medizinischer Versorgungsleistungen im Alter; EQ-5D, EuroQol Group; RS-13, the 13-item Resilience Scale.

To avoid the loss of data at baseline and follow-up assessments, the assessors will contact patients whose questionnaires are missing by phone in intervals of 10 to 14 days. For patients who choose to discontinue the trial or deviate from the intervention protocol, a final telephone survey will be conducted. The follow-up calls by the assessors follow a standard operation procedure (SOP) that was defined to ensure a structured and systematic procedure in terms of subsequent collection of missing data via telephone. This approach is restricted to items that do not relate to the patient’s psychological background, with the exception of the PHQ-9 as primary outcome. If answers to more than one item in the PHQ-9 are missing, the PHQ-9 will be reassessed completely by the data management team (in this case, other data regarding health status will be declared invalid). Any revision has to be signed by the assessor with their name and date. Only completed questionnaires will be passed on to data entry.

According to the SOP, data will be entered corresponding to the defined coding plan in the EpiData Entry Client (Version 1.4.2; EpiData Manager Version 1.4.2 for data export) [46]. Instead of running a double data entry procedure, the entered data will be completely (100%) checked and, if necessary, corrected by a second person on the data management team. Data export files (Stata Version 12.1 and SPSS Statistics Version 21 [33, 47]) from both study centers will be centrally collected at the study center in Hamburg for statistical analysis.

As after assignment the research stuff is not blinded, no external data monitoring committee is needed, and data concerning patient safety and treatment efficacy can be monitored internally. Similarly, auditing of the trial conduct will be administered by the research staff: the data management teams in Freiburg and Hamburg will monitor the completion of the questionnaires, while the study coordinators will ensure adherence to the intervention protocol.

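### Retaking an incomplete PHQ-9 voids the patient's other health-status answers, an avoidable loss in secondary and possibly economic outcomes

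*Protocol article*

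**What the plan says.** The rules stand in the protocol article, Outcome measures and assessment, Assessment, in the text after Table 2. That paragraph opens with its purpose: "To avoid the loss of data at baseline and follow-up assessments".

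- **Trigger.** "If answers to more than one item in the PHQ-9 are missing, the PHQ-9 will be reassessed completely by the data management team"
- **Consequence for everything else.** "in this case, other data regarding health status will be declared invalid"
- **Limit on telephone completion.** "This approach is restricted to items that do not relate to the patient’s psychological background"; the PHQ-9 is the only exception named.
- **Data entry.** "Only completed questionnaires will be passed on to data entry"
- **Discontinuers and deviators.** "For patients who choose to discontinue the trial or deviate from the intervention protocol, a final telephone survey will be conducted"

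The Statistical analysis section treats missing items by each instrument's manual. Where no manual rule exists, the EM algorithm "will be used to impute up to 30% of missing item responses". A patient who misses a whole measurement point is imputed by EM from baseline and 6-month data. The primary analysis covers all randomized patients.

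**The concern.** The second rule removes data that were actually observed. The patient has returned a form with, say, a full anxiety scale and a full EQ-5D. These are declared invalid because two boxes on another scale were left empty. The paragraph exists to prevent data loss, and this rule produces it, at baseline as well as at follow-up.

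Three things are at stake.

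- **Recovery.** Psychological items other than the PHQ-9 may not be collected by telephone, so a voided GAD-7 could not be regained by that route.
- **Economic evaluation.** If EQ-5D counts as health status, the quality-of-life measure behind the cost-effectiveness aim is exposed.
- **Selectivity.** Patients who leave PHQ-9 items blank may differ from those who do not, so the loss need not be random. The documents hold no data on this.

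A voided scale beside a recovered PHQ-9 also fits neither missing-data rule clearly. It is more than 30% of that scale's items, yet it is not a whole measurement point.

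**Working it through.** **1. What the rule touches.** The primary outcome is the PHQ-9, and the retake restores it. The rule therefore does not reduce the number analysed for the primary outcome. Table 2 lists the other instruments. By content, GAD-7, the pain scale, EQ-5D and the comorbidity index could each be called health-status data. The article does not say which are meant.

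**2. Cost in precision for a continuous secondary outcome.** The plan has no figure for this rule, so there is none to reproduce. Inputs from the Sample size section: 300 patients, 60 GPs, intraclass correlation 0.10, 15% loss to follow-up, two-sided alpha 0.05, power 0.80. Assumptions: the same intraclass correlation applies to the secondary outcomes, clusters are of equal size, and 0%, 5%, 10% or 20% of records are voided. The documents give no voiding rate.

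Start: 300 × 0.85 = 255 patients.

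Design effect: DE = 1 + (m − 1) × 0.10, with m = N/60.

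Detectable standardised difference: (1.960 + 0.842) × √(4 × DE / N).

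| Voided | N | m | DE | Detectable difference |
|---|---|---|---|---|
| 0% | 255 | 4.25 | 1.325 | 2.802 × √(5.300/255) = 0.404 |
| 5% | 242.25 | 4.04 | 1.304 | 2.802 × √(5.215/242.25) = 0.411 |
| 10% | 229.5 | 3.83 | 1.283 | 2.802 × √(5.130/229.5) = 0.419 |
| 20% | 204 | 3.40 | 1.240 | 2.802 × √(4.960/204) = 0.437 |

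Even at 20% voided, the detectable difference grows by only about 8% (0.437/0.404 = 1.08). Precision is a minor cost. The stronger reasons against the rule are that the loss may be selective and that it is unnecessary.

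**3. Meaning of a completed questionnaire.** The data-entry sentence follows the telephone queries and the signed revisions. Under Recruitment of patients, the article uses the same term for forms that are still to be checked for completeness. The PHQ-9 retake starts only at the second blank item, so one blank is tolerated even on the primary instrument. Both points favour reading the term as returned and query-closed. On that reading, partly blank forms reach the database and the item-level rule can work. Read literally, they would not.

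**4. The final telephone survey.** Assessment sends questionnaires at baseline, 6 and 12 months to both groups and makes no exception for deviators. Blinding says that assessors contact patients in both arms repeatedly. Sample size and Statistical analysis include all randomized patients. Against this, the word *final* and the grouping of deviators with patients who leave the trial suggest an end of follow-up that the article never states.

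**The case against.** The best defence of the voiding rule is timing. A PHQ-9 retaken by telephone may be days or weeks later than the mailed answers, and the investigators may want all instruments to refer to one moment. The article does not give this reason. It would also not require deletion, because each secondary outcome is modelled on its own score and a date can be recorded.

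Three parts of the defence stand. The article is condensed and refers to a standard operating procedure that is not shown, so the scope of health status may be narrow. Resource use (FIMA) measures service utilization and is doubtful as health status, so one cannot say that every other scale is lost. The trigger is blank items, not a high score, so a link between the loss and depression is possible but not shown.

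A reader might infer two stronger points. The first is that a form with one blank GAD-7 item can never be entered, which would contradict the item-level imputation rule. The article's own use of the term, and its tolerance of one blank PHQ-9 item, do not support this. The second is that deviators receive the telephone survey in place of the 6- and 12-month questionnaires, so that intention-to-treat is broken and the remission difference biased. No sentence says so. Nor can a bias be sized: no deviation rate is given, the 25.0% remission rate belongs to the whole intervention group, the PHQ-9 may be taken by telephone, and the imputation uses the patients' own earlier data.

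**Conclusion.** The point holds for the voiding rule. As written, it discards answers validly given on other instruments because the PHQ-9 was incomplete. The harm is avoidable and possibly selective loss in secondary outcomes, and in the economic evaluation if EQ-5D is covered. The primary outcome is not lost.

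The size is uncertain because no frequency is stated. Under assumed voiding rates of 5% to 20% and a common intraclass correlation of 0.10, the detectable standardised difference rises from 0.40 to 0.41–0.44. That is modest.

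The completed-questionnaire sentence and the final telephone survey are wording points only. The second sits awkwardly beside the intention-to-treat plan and should be reconciled with it. No contradiction, intention-to-treat breach or effect-size bias is established for either.

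**What to change.** **Main change.** Delete the rule that declares other health-status data invalid. Keep all returned answers with their own completion date, and flag a retaken PHQ-9 by mode (telephone) and date. The downside is a small time gap between instruments for some patients. The flag lets a sensitivity analysis check whether it matters.

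**Wording, data entry.** State that completed questionnaires are forms that have been returned and whose queries are closed, blanks included, so that the item-level missing-data rule can apply.

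**Wording, deviators.** State that deviating from the intervention does not by itself end the 6- and 12-month assessments, and separate these patients from those who discontinue the trial. This brings the sentence into line with Sample size, Assessment and Statistical analysis.

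**Cost.** A few sentences in the operating procedure and analysis plan, and two extra fields (mode and date) at data entry. The article reports recruitment as still in progress, so the change could still protect later returns. If discarded answers are never entered, the analysis cannot restore them.
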